##### Subjective appraisal & recovery: quality of life

The Manchester Short Assessment of Quality of Life (MANSA-16) [72] will be administered to assess Quality of life (QoL). With twelve 7-point Likert-type items and four *yes/no* items, participants can indicate their level of satisfaction with respect to several life-domains, including social contact, psychological wellbeing and housing. The MANSA has been demonstrated to have good internal consistency [73]. Higher scores indicate higher QoL.

##### Subjective appraisal & recovery: symptomatic, somatic and personal recovery

The Integrale Herstel Schaal (IHS) [74] will be used to assess recovery. This 13-item instrument is designed to assess recovery among people with an SMI and is suited for the purpose of Routine Outcome Monitoring (ROM). The IHS is a multidimensional instrument that matches the definition of recovery from the patient-perspective and includes the assessment of symptomatic, somatic, social/societal and personal recovery. To our knowledge, the IHS in itself has not been tested for its psychometric properties as the IHS is an assembly of items from existing ROM-instruments, among which the functional remission scale [75], the Health of the Nations Outcome Scales (HoNOS) [75] and the INSPIRE [76]. To be able to compute IHS total scores, HoNOS items retrieved from patient files will be used in addition to the items included in the interview.

##### Subjective appraisal & recovery: personal recovery

The Dutch national recovery scale (in Dutch “Nationale Herstelschaal”) [77], an adaptation of the Questionnaire about the Process of Recovery (QPR) [78], will be used to assess specifically personal recovery. This instrument measures personal recovery on the basis of 26 Likert-type items ranging from 1 = *strongly disagree* to 5 = *strongly agree.* Examples of items are *I feel good about myself*, *My life has a purpose*, *I can manage to actively engage life* and *I have trust in others*. A total score can be computed with a maximum of 4 missing answers and scores range from 26 to 100. Higher scores indicate higher personal recovery. The NHS has been shown to be a user-friendly, reliable and valid instrument [77].

##### Health: physical health

With respect to physical health, both general perceived health (the extent to which people suffer from physical complaints) and physical limitations in daily functioning will be assessed using two subscales of the RAND SF-36 Health Survey [79]. The subscale general health measures self-perceived health, ranging from 1 = *excellent* to 5 = *bad*. The subscale physical functioning measures the level of limitations in daily functioning using 10-items (e.g., lifting groceries, climbing a few stairs) with score categories 1 = *severely limited* and 3 = *not limited*. The subscale physical functioning has an internal consistency of Cronbach’s α = .92, and good test-retest reliability after 2 (r = .82) and 6 months (r = .72), respectively. The sensitivity to change of the general perceived health subscale is satisfactory and it has good convergent validity with other scales. The psychometric properties are sufficient [80].

##### Health: perceived needs for care

The Camberwell Assessment of Need Short Appraisal Schedule (CANSAS) [81], a short version of the Camberwell Assessment of Need (CAN) [82], is used to assess need for care and support. The CANSAS consists of 25 items that concern care needs and care reception in 25 distinct life-domains (e.g., housing, intimate (partner) relations, psychological wellbeing, finances). For each domain, participants indicate if they have a need for care and the extent to which the need is provided for. Each of the domains can be scored with 0 = *no need*, 1 = *met need for care* and 2 = *unmet need for care*. Additionally, for needs for care that are met, participants can indicate if care/support is provided by formal and/or informal care providers. Psychometric properties of the CANSAS were demonstrated to be satisfactory concerning, amongst others, test-retest reliability and interrater reliability [81, 83].

##### Health: psychiatric symptomatology (symptom severity and psychiatric complaints)

The 24-item version of the Brief Psychiatric Rating Scale (BPRS-E) [84–87] will be administered to assess psychopathology severity (and is used to validate the inclusion of participants in the not-in-care group based on the SMI-criteria). In this version of the BPRS [88] 14 items are administered during the interview and 10 are scored by the interviewer after a finished interview. Each item is scored on an anchored 7-point scale varying from 1 = *not reported/not observed* to 4 = *moderate* and 7 = *very severe*. Scores indicate the presence and severity of psychiatric symptoms observed during the interview or reported by the participant with scores 2–3 indicating non-pathological intensity and scores 4–7 indicating pathological intensity of the symptom at hand. Besides the calculation of a total BPRS-score, the following subscales can be calculated: positive symptoms, negative symptoms, depression and anxiety, and disorganization. The BPRS and its subscales are suited for clinical and epidemiological purposes, sensitive for change [89, 90] and overall good psychometric properties of the BPRS have been demonstrated [91].

#### Administrative data

On the basis of informed consent, administrative data from all participants will be retrieved from their patient and/or client files at either Arkin, GGZ inGeest and/or the service providers where “not-in-care” participants will be recruited. These data concern:Assessments of general functioning, routinely assessed by mental health services with the 12-item Health of the Nations Outcome Scale (HoNOS) [75]. The HoNOS was developed specifically for the simple, reliable and valid routine assessment of the psychological and social functioning of people with a psychiatric disorder. The HoNOS proved to be sensitive to change. The 12-item HoNOS consists of the subscales behavior problems, psychological and somatic limitations, symptomatology and social problems. HoNOS scores will be considered only if they were obtained 6 months before or after the date of the interview.Type and date of crisis-interventions including mental health crisis intervention by Acute care service of the mental health providers as well as the interventions by the Public Health Service Amsterdam [92]; evictions from (social) housing as registered by the social housing providers and the municipal residence registration; compulsory house cleaning and disinfections executed by the PHS and police contacts as either victim or suspect as registered by the police department.health care related patient data from Arkin and GGZ inGeest with respect to psychiatric diagnoses, therapy compliance and contacts with other care providers;administrative data about the care/support process from other social support/care providers involved, as self-reported by participants;registry data from municipal services (e.g., Amsterdam’s social service (in Dutch: “Werk, Participatie en Inkomen”), the care and nuisance hotline (in Dutch: “Meldpunt zorg en woonoverlast”).

### Primary study outcomes

The study has three primary outcome measures: recovery, societal participation, and quality of life. With respect to recovery, the total score of the National Recovery Scale [77] will be used. Concerning societal participation, two separate indicators will be involved: 1) having formal work/daytime activities (yes/no) and 2) the total score of the Social Exclusion Index for Health Surveys (SEI-HS) [55]. Last, quality of life will be operationalized according to the total score of the MANSA-16 [72].

### Bias

Some types of bias will need to be taken into account when interpreting the results.

We set out to include at least 30% of the population with an SMI living within the selected quarters in the city of Amsterdam, recruited from the two main mental health service providers and several primary care- and social support services. Both the selection of quarters and the recruitment method, can introduce selection bias. Although we only include about 8% of the estimated total SMI-population in Amsterdam, we assume that in spreading the selected quarters over the seven residential city districts and recruiting within the two most populated quarters within those districts, we include a representative sample of the SMI-population in Amsterdam. In addition, it is unlikely that the population in other (smaller) quarters differs systemically from the population in the selected quarters on the background- and outcome measures of this study: social-economical and background characteristics of the general population do not vary widely within quarters (in contrast to variance between quarters). As the SMI-population moves within the same (social) housing pool as the general population, selection bias due to sampling in specific quarters is expected to be limited.

### Statistical methods

All cross-sectional socio-demographic data from both baseline and follow-up measurements will be reported in terms of percentages, means with standard deviations, and quartiles. In addition, all study measures (from the instruments administered and from the registry data) will be analyzed descriptively to provide estimates of the relevant proportions within our study population with respect to these variables as (partial) answers to research questions 2, 4 and 5.

In addition, to provide information on the association between experienced need, and the primary outcome variables (research question 1), data collected at baseline will be analyzed using multivariate regression with recovery, societal participation and quality of life as separate dependent variables and total scores on the CANSAS (i.e. number of unmet needs for care), discrimination scale, stigma scale and victimization as independent (predictor) variables. Any potential mediating effects on the associations between predictors and outcomes variables will be investigated by adding age, sex, psychiatric symptoms (BPRS-E), harmful/dependent alcohol and/or drug use (AUDIT and DUDIT respectively), physical health (RAND SF-36) and city-districts as covariates in these analyses.

To answer research question 2, relationships between the outcome measures and distinct CANSAS items, registry data concerning the care process (i.e. treatment compliance, therapeutic alliance, frequency and timeliness of care consults and self-reported support for social problems) from mental health institutions and support/welfare organizations will mainly be reported in terms of percentages and, for obvious comparisons between groups, using regression models and chi-squared tests. Their associated proportion of variance explained Nagelkerke’s R^2^, Phi for 2 × 2 tables and Cramer’s V for larger than 2 × 2 tables will be reported. Phi and Cramer’s V will be interpreted as indicating no or very weak (> 0), weak (>.05), moderate (>.10), strong (>.15) or very strong (>.25) association between variables [93]. Eta-squared and Cohen’s D will be interpreted as very small (0–.19), small (.20–. 49), moderate (.50–.79), large (.80–1.20), very large (1.20–1.99) or huge (2.0) [94].

Research question 3 will be analyzed using data from the baseline and follow-up measurement by means of generalized linear mixed models with repeated measurements of recovery, quality of life and societal participation as dependent variables. The time between both measures will be included as a within-subjects factor. The same set of predictor variables as mentioned above will be treated as time-dependent independent variables. Additionally, the total score on Brugha’s life-events questionnaire will be included as a potential mediator to assess the effect of having experienced adverse life-events in the time period between baseline and follow-up on the associations between predictor and outcome variables. All variables will be checked for potential outliers. Missing values will be dealt with appropriately. Participants with > 80% missing values on all items will be deleted from the final dataset. For most measures, descriptive analyses will be carried out and the proportion of missing values will be reported for each variable of interest. In subsequent statistical analyses, values missing at (completely) random (i.e. MAR and MCAR) will be deleted pair wise. Values that are not missing at random (NMAR) will be imputed with either the mean, median or using multiple imputation, whichever is most appropriate. Concerning outcome measures that are a sum score of items, instructions from the instrument developers will be followed (e.g., impute missing values with the mean value of the non-missing items and calculate a sum score only if < 10% of items are missing).

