The research program is modular. It consists of multiple interrelated research projects. Each of these projects addresses deinstitutionalization from one of the aforementioned perspectives. The current study protocol applies to the ‘client study’ of the program, that focuses on the perspective on deinstitutionalization from its main stakeholder: community-dwelling adults with an SMI. More specifically, the protocol lays out the study design by means of which a representative research cohort of people with an SMI in Amsterdam will be assembled (i.e. inclusion and exclusion criteria) and followed over time. Additionally, the protocol describes the process of participant recruitment, the instruments that will be administered, the study’s primary outcome measures and the statistical analyses that will be performed. Furthermore, the protocol specifies how the following research questions will be addressed:Which trends in the development of community-dwelling people with an SMI concerning their quality of life, recovery, daily functioning and societal participation can be observed over the course of time?Which needs of community-dwelling people with SMI are most important with respect to their recovery and societal participation?How are these needs addressed and accommodated by formal and informal providers of ambulatory care and support?How can the provision of community-based ambulatory care for people with an SMI be described with respect to treatment compliance, therapeutic alliance and frequency/timeliness of care consults?What is the prevalence and incidence during follow-up of personal crises and escalations, including psychological crises, compulsory (clinical) treatment and victimization, among this population?

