## Methods

### Study design

The Deinstitutionalization Amsterdam Client-study is a cohort study that started in December 2017. The study is planned to include approximately 800 adults with an SMI. The study population is designed to be representative for the target population of community-dwelling adults with an SMI at the city level, the level of the city-districts and the level of the city’s quarters (i.e. combined neighborhoods). To acquire a better insight into developments in the functioning and recovery of community-dwelling adults with an SMI and their associated needs for care/support, a comprehensive set of measurement instruments will be administered twice, with a two-year time interval, by means of semi-structured interviews. Also, the occurrence of adverse life-events during follow-up will be associated with developments in people’s functioning (i.e. social recovery and societal participation) over the course of time. Additionally, information about the care processes during that time will be retrieved from participants’ patient files.

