**Fig. 1 Fig1:**
[figure not shown]
Flowchart of the composition of the target population from which the study population will be sampled

In-care and not-in-care participants were recruited consecutively, to avoid duplicate recruitment attempts. The recruitment period of the in-care group, and the LZA-cohort in parallel, was December 2017–January 2021. Recruitment of participants in the not-in-care group was executed between January 2021 and January 2022. At baseline, participants were interviewed about their functioning with respect to important aspects of life (see instruments) by a pool of trained interviewers. All participants will receive a financial compensation of €15, for each interview. Interview data will be matched with information retrieved from patient files that concerns important aspects of the care process. Follow-up interviews will be held two years after the first interview and will consist of the same set of instruments as administered during interview 1. The recruitment period of follow-up interviews of the in-care cohort and the LZA-cohort will start in December 2019 to end in June 2022. Not-in-care participants will be approached to participate in interview 2 between January and September 2023.

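### Incidence of crises during follow-up is to be answered with proportions, although the interview windows leave late recruits less than the stated two years

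*Protocol article*

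**What the plan says.** All references are to the protocol article.

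- Background, list of research questions: the fifth asks about "prevalence and incidence during follow-up of personal crises and escalations", and names psychological crises, compulsory treatment and victimization among them.
- Statistical methods, first paragraph: all instrument and registry measures are analysed descriptively, to give "estimates of the relevant proportions within our study population with respect to these variables as (partial) answers to research questions 2, 4 and 5". No rate, person-time denominator, fixed horizon or censoring rule is given for question 5. The time between measurements enters only the mixed models, which are assigned to question 3.
- Study design: the instruments are "administered twice, with a two-year time interval", and care-process information is to be retrieved for that same time.
- Participants, text after Figure 1: "Follow-up interviews will be held two years after the first interview". Baseline recruitment ran from December 2017 to January 2021 (in-care and LZA) and from January 2021 to January 2022 (not-in-care). For follow-up, "The recruitment period of follow-up interviews of the in-care cohort and the LZA-cohort will start in December 2019 to end in June 2022" and "Not-in-care participants will be approached to participate in interview 2 between January and September 2023".
- Administrative data: the registry items include "Type and date of crisis-interventions".

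**The concern.** A proportion of people with an event estimates incidence over a defined period only if everyone is observed for that period, or if shorter observation is handled in the estimate. Here the stated calendar makes observation unequal, and nothing in the stated analysis allows for it. Two people at the same risk then contribute differently according to when they were recruited. The resulting figure is not a two-year risk, although the two-year design invites that reading. It also cannot be set cleanly beside outside figures that have a defined time base.

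Question 5 is not one of the primary outcomes, but incidence is one of the five questions the study sets out to answer.

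**Working it through.** **Inputs.** The recruitment and follow-up windows come from the Participants section. I take months as running from their first to their last day, and the window close as the latest interview date. The protocol gives no event rate, so a constant rate is assumed: 0.20 first events per person-year, with a range of 0.05 to 0.50.

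**Step 1: reproduce the two-year interval.** It matches the opening dates: 1 December 2017 to 1 December 2019 is 24.0 months (in-care, LZA), and 1 January 2021 to 1 January 2023 is 24.0 months (not-in-care). It does not match the closing dates.

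**Step 2: longest possible follow-up for the last recruits** (window close minus baseline date).

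- In-care/LZA: 31 January 2021 to 30 June 2022 = 16.9 months (17.9 if recruited on 1 January 2021).
- Not-in-care: 31 January 2022 to 30 September 2023 = 19.9 months (20.9 if recruited on 1 January 2022).

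**Step 3: share of the recruitment period that cannot reach 24 months.** The last feasible baseline date is the window close minus 24 months.

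- In-care/LZA: after 30 June 2020, 7.1 of 38.0 months = 19%.
- Not-in-care: after 30 September 2021, 4.0 of 13.0 months = 31%.

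These are also shares of participants if accrual was uniform (assumption).

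**Step 4: effect on an individual's proportion at equal risk.** Proportion with an event = 1 − exp(−rate × months/12).

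| Assumed rate per person-year | 17 months | 20 months | 24 months |
|---|---|---|---|
| 0.05 | 6.8% | 8.0% | 9.5% |
| 0.10 | 13.2% | 15.4% | 18.1% |
| 0.20 | 24.7% | 28.3% | 33.0% |
| 0.30 | 34.6% | 39.3% | 45.1% |
| 0.50 | 50.8% | 56.5% | 63.2% |

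**Step 5: effect on the cohort figure.** Suppose each person is interviewed at 24 months or at window close, whichever is first, and accrual is uniform.

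- Mean follow-up, in-care/LZA: 24 − (7/38) × 3.5 = 23.4 months.
- Mean follow-up, not-in-care: 24 − (4/13) × 2 = 23.4 months.

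Averaging the Step 4 formula over recruitment dates gives:

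| Assumed rate per person-year | In-care/LZA | Not-in-care | True two-year risk |
|---|---|---|---|
| 0.10 | 17.7% | 17.7% | 18.1% |
| 0.20 | 32.2% | 32.3% | 33.0% |
| 0.30 | 44.2% | 44.2% | 45.1% |
| 0.50 | 62.1% | 62.2% | 63.2% |

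The shortfall is about 0.4 points at 0.10, 0.7 at 0.20, 0.9 at 0.30 and 1.0 to 1.1 at 0.50. The two cohorts differ by no more than about 0.1 point.

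**The case against.** The other side has four points.

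- **The cohort-level effect is small.** Step 5 shows this, and it stands. A reader might infer a much larger problem from the width of the not-in-care window. A January 2021 recruit seen at 32 months against a January 2022 recruit seen at 12 would give 41% against 18% at 0.20 per year, more than twofold. The document does not support that reading. It would require seeing the earliest recruits last and the latest recruits first, against the stated two-year rule, under which January 2021 recruits are seen at about 24 months. A claim that the two cohorts could not be compared fails for the same reason.
- **Registry observation need not stop at interview 2.** No extraction end date is stated, and a fixed 24-month extraction would remove the problem. This is fair. However, Study design links care-process retrieval to the time between interviews, and no fixed extraction period is given. Self-reported victimization has its own recall period, which nothing ties to the interview interval.
- **The sentence on proportions is general.** It offers only partial answers, and question 5 also asks for prevalence, for which proportions are right. This stands for prevalence and fixed-recall items. It also means one cannot infer that repeat crises will be counted once; the text does not say so.
- **An article may leave the incidence estimator to a fuller plan.** This would settle the matter if the article were silent. It names a type of estimate for question 5, though, and its own dates contradict the equal follow-up on which that estimate depends.

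**Conclusion.** The point holds in a limited form. The windows contradict the two-year interval for about 19% of the in-care/LZA recruitment period and about 31% of the not-in-care one. This part is calendar arithmetic and needs no assumption about event rates. For those late recruits, the named estimate does not give incidence over a common period.

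The dependence on recruitment date is real: 25% at 17 months against 33% at 24 at the assumed 0.20 per year. Overall and between-cohort distortion is small, under 1 point at rates of 0.10 to 0.30 and about 1 point at 0.50.

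The sizes rest on a constant event rate, uniform accrual, event observation ending at interview 2, and interviews at two years wherever the window allows. The change is worth making because the quantity asked for is not the one the stated method delivers, and the better method is nearly free.

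**What to change.** 1. For dated registry events (such as crisis interventions, evictions and police contacts), define time at risk from the baseline interview to a stated end of observation, including for people who have no second interview.
2. Report events per 100 person-years, or cumulative incidence at a common 24 months (Kaplan-Meier) with shorter observation censored. Alternatively, extract the registries for a fixed 24 months from baseline for everyone. State whether first or all events are counted.
3. Keep proportions for prevalence and for items with a fixed recall period.
4. Reconcile the two-year interval with the follow-up windows: either state that late recruits will have a shorter interval, or correct the dates. A full 24 months for the last recruits would need windows reaching January 2023 (in-care/LZA) and January 2024 (not-in-care).

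Regression with log person-time as offset is optional for a descriptive question. The cost is a few sentences and slightly more analysis work. Crisis-intervention dates are already among the planned registry items and interview dates will be known, so no new data are required, though a fixed 24-month extraction may mean a later extraction date.

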**Methods:**

A cohort design will be used. A representative sample of community-dwelling adults with an SMI, including those in care (*n* = 650) and not in care (*n* = 150), will be followed over time. During a two-year time period, participants will be interviewed twice using a wide-ranging set of validated instruments. Interview data will be matched with administrative data about the care process, as retrieved from their patient files. Primary outcomes are changes over time in recovery, societal participation and quality of life, controlled for the occurrence of adverse life-events during follow-up. Additionally, prevalence estimates of and associations between social functioning, safety and discrimination, substance use and health indicators will be investigated.

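### Adding age, sex, symptoms, substance use, physical health and district as covariates to a baseline regression cannot show mediation, which is the stated purpose

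*Protocol article*

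**What the plan says.** In the protocol article, Statistical methods, the first association analysis uses one wave only: "data collected at baseline will be analyzed using multivariate regression with recovery, societal participation and quality of life as separate dependent variables". The predictors are "total scores on the CANSAS (i.e. number of unmet needs for care), discrimination scale, stigma scale and victimization as independent (predictor) variables". The section then gives a purpose and a method together: "Any potential mediating effects on the associations between predictors and outcomes variables will be investigated by adding age, sex, psychiatric symptoms (BPRS-E", followed by harmful or dependent alcohol and drug use (AUDIT, DUDIT), and ending with "physical health (RAND SF-36) and city-districts as covariates in these analyses". It describes no model of predictor on mediator, no indirect effect and no time ordering. It does not separate confounders from candidate mediators.

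For the two-wave mixed models, the same section says that "the total score on Brugha’s life-events questionnaire will be included as a potential mediator". The Methods paragraph of the abstract describes the primary outcomes as changes over time, "controlled for the occurrence of adverse life-events during follow-up".

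The section on adverse life-events says that the instrument records lifetime and past-year events. Study design puts the two interviews two years apart.

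**The concern.** A mediator lies on the path from predictor to outcome, so the predictor must be able to affect it. The covariate list mixes variables that cannot meet this condition (age, sex), one that is unlikely to (district) and several that might (symptoms, substance use, physical health). All are given the same purpose and the same procedure.

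If the plan is followed as worded, a coefficient that shrinks when age or sex is added would count as evidence on mediation, when it can only reflect adjustment. For symptoms, substance use and health, the reader could not tell which of the two had occurred. The research program asks how care and support are best provided, so a mistaken statement about mechanism could carry into advice on services.

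**Working it through.** The plan gives no figure to reproduce here, so the check is by logic and a short illustration.

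**Step 1. Can each listed variable be a mediator of unmet needs, discrimination, stigma or victimization?**

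| Variable | Can the predictor cause it? | Role it can take |
|---|---|---|
| Age, sex | No | Confounder (or effect modifier, if interactions are fitted) |
| City-district | Possible, since a person may move after victimization, but less plausible than the reverse | Confounder or contextual factor |
| BPRS-E, AUDIT/DUDIT, physical health | Yes, but they may also cause the predictor | Mediator or confounder |

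**Step 2. Can the stated regression tell a mediator from a confounder?** Let X be the predictor, Z the added variable and Y the outcome, with X and Z standardized. The paths are assumed, not taken from the documents: X–Z = 0.4, Z→Y = -0.4, direct X→Y = -0.3.

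- *Z is a mediator (X→Z→Y).* Without Z, the coefficient of X is direct + (X→Z)(Z→Y) = -0.3 + (0.4)(-0.4) = -0.46. With Z it is -0.30.
- *Z is a confounder (Z→X and Z→Y).* Without Z, the coefficient of X is direct + corr(X,Z)(Z→Y) = -0.3 + (0.4)(-0.4) = -0.46. With Z it is -0.30.

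The attenuation is (0.46 - 0.30)/0.46 = 0.16/0.46 = 35% in both cases.

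A simulation agrees (4,000 replicates, n = 800, the planned size in Study design). The mean coefficient went from -0.460 to -0.301 with Z as confounder and from -0.460 to -0.300 with Z as mediator. A larger sample would not help, because the two structures imply the same regression.

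**Step 3. Reach.** There are four predictors. Primary study outcomes lists four indicators: the National Recovery Scale, formal work or daytime activities, the SEI-HS and the MANSA-16. If both societal participation indicators are modelled, that is 4 × 4 = 16 baseline associations.

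**Step 4. The life-events score in the two-wave model.** A path from baseline predictor to interval event to follow-up outcome is plausible, so calling the score a potential mediator is not wrong in itself. Entering it as a model term is still not a test of mediation, for the reason in Step 2.

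The measurement window also fits poorly. At follow-up, a past-year count misses the first of the two years, while a lifetime count includes events before baseline. The example items in the adverse life-events section include severe illness and violent victimization, which overlap with the physical health covariate and the victimization predictor.

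**The case against.** The strongest defence is that entering these covariates is sensible adjustment, that the text speaks only of investigating potential effects, and that a condensed article may leave an indirect-effect procedure to a fuller plan. The first part stands: the models are reasonable as adjusted models, and the fault lies in the role assigned to the covariates and the inference drawn. The rest does not remove the point. The article states a purpose and a method that do not fit each other, and no further detail could make age or sex a mediator. If moderation was meant, covariates without interaction terms would not test that either.

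A reader might infer more than the documents support:

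- *The headline results are unadjusted for age, sex and district.* The text says these variables will be added, and nothing makes the model without them the main result.
- *A proportion mediated will be published.* No such statistic is planned. The 35% above comes from assumed paths and is not an estimate for this study.
- *Life events are a confounder.* This is not established. The recall windows and overlapping items give no clean time order, and a mediating path remains plausible.
- *The abstract contradicts the statistics section on life events.* Controlling for the score and including it as a potential mediator both describe entering it in the model. The difference is one of interpretation and too slight to count as a contradiction.
- *Age, sex and district are tested as mediators again in the mixed model.* That text carries over the predictors and names only the life-events score as a mediator.

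**Conclusion.** The point holds as an error of stated purpose and interpretation. For age and sex, the mediation label is wrong by logic alone. For district, it is implausible but not impossible. For symptoms, substance use and physical health, mediation is possible, but the planned single-wave regression cannot distinguish it from confounding. The same limit applies to reading the life-events term in the mixed model as a test of mediation.

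The fault reaches up to 16 baseline associations. No numerical bias can be derived from the documents. The conclusion does not depend on sample size, effect size or significance level. It rests on the usual meaning of a mediator and on all baseline variables being analysed from one wave.

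**What to change.** 1. Name age, sex and city-district as confounders and enter them in every predictor–outcome model.
2. Report a second model adding BPRS-E, AUDIT/DUDIT and physical health, labelled *further adjusted*. State that a change in coefficient will not be interpreted as mediation.
3. In the two-wave analysis, report change over time both with and without the life-events score, and do not present its inclusion as a test of mediation.
4. If a mediation claim is wanted, limit it to plausible mediators named in advance. Use the two waves with time ordering and estimate an explicit indirect effect. For life events, state as a limitation that lifetime and past-year recall does not match the two-year interval.

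Items 1 to 3 cost a change of wording and a few extra models on variables already planned. Item 4 is optional. It needs a separate analysis and, for life events, remains limited by the recall windows.
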